## 3.10. Statistical consideration

### 3.10.1. Analysis of population and missing data

**Full Analysis Set (FAS):** According to the intention-to-treat (ITT) principle, this study aims to include as many participants as possible. Participants who did not complete all three doses of vaccination will be excluded.

**Per-Protocol Set (PPS):** Based on the FAS population, participants with poor compliance will be excluded. Specifically, this set excludes individuals who participated in follow-up no more than six times.

**Safety Set (SS):** Participants with at least one vaccination record and measured AEs/SAEs correspondingly.

**Missing Data Processing:** The missing data on demographic information, safety indicators, and immunogenicity indicators for the FAS and PPS populations will not be imputed.

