### 3.10.2. Statistical methods

**Principles of statistical analysis:**

All statistical analyses were performed using IBM SPSS (version 26).

Demographic analysis will be performed in FAS population, the primary analysis (safety) will be performed in the SS population, and the secondary analysis (immunogenicity) will be performed both in the FAS and PPS population.

The Kolmogorov-Smirnov test was used to evaluate the distribution types. Non-normally distributed and ordered data are represented by the median (range). Measurement of pseudovirus 50% neutralization titers (pVNT_50_s) are represented by geometric means. Pearson’s chi-square test, continuity correction, and Fisher’s exact test were used to check the proportion of the count data.

The Mann-Whitney U test and paired t-test were used to compare differences between groups, the Wilcoxon rank-sum test was used to compare intragroup differences, and the nest t-test was used to compare unmatched groups. We displayed the median values of each group in the figures using GraphPad Prism 8 and estimated the differences based on the 95% confidence interval (CI).

Baseline characteristics were screened using univariate logistic regression, and the significantly different factors (*P*_value<0.1) were further analyzed using multivariate logistic regression. The analysis results are presented using an OR combined with a 95% CI (lower–upper) in the table.

In correlation analysis, the Pearson correlation test was used to process normally distributed datasets, while the Spearman rank correlation test was used to process non-normally distributed datasets. An absolute R value>0.5 indicated a strong correlation, whereas an absolute R value≤0.5 indicated a weak correlation.

The hypothesis test was bilateral, and a *P*_value<0.05 was considered statistically significant.

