**Demographic analysis:**

The analysis of baseline demographic information will be based on the FAS population.

This includes a statistical description and comparison of baseline demographic information (including age, gender, BMI, laboratory test indices, and comorbidities) to measure comparability between the two groups. Summarized statistical data will be used based on the properties of the variables (continuous or categorical).

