**Breakthrough infection analysis:**

The population for breakthrough infection analysis will be based on the FAS population and exclude participants whose SARS-CoV-2 infection status during the end of the 2022 pandemic cannot be confirmed through follow-up. The **Demographic analysis** will be performed as above.

(1) Proportion of different breakthrough infection states

Based on follow-up data, the status of breakthrough infections among the participants will be statistically described, and the infection rate will be used as an intergroup categorical variable for comparison using Pearson’s chi-square test.

(2) Proportion of different types of breakthrough infection symptoms

The symptoms of symptomatic infected individuals will be statistically described and displayed as intergroup categorical variables.

(3) Duration of breakthrough infection symptoms (days)

The duration of symptoms will be statistically described using the duration as the classification criterion (if longer than 7 days) and compared as an intergroup classification variable.

(4) Correlation between infection and antibody titers

The infection status within the two groups will be statistically described, and the corresponding antibody titers will be presented as continuous variables. An intragroup comparison will be performed using the Mann–Whitney U test, and the corresponding medians and 95% CIs will be calculated.

(5) Correlation between symptom severity and antibody titers

Based on the classification criteria of whether the duration of symptoms is longer than 7 days, whether there is accompanying fever, and whether there are multisystemic symptoms, the infection symptoms of the two groups will be statistically described. The corresponding antibody titers will be considered continuous variables; the Mann–Whitney U test will be employed for the intragroup comparison, and the corresponding medians and 95% CIs will be determined .

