# 7. APPENDICES

## *7.1 Revision History*

| **Version** | **Date** | **Amendment Text** | **Description** |
| --- | --- | --- | --- |
| 1.1 | March 6, 2020 | **Vaccination plan adjustment:**  The original statement “the participants will complete two doses of inactivated COVID-19 vaccine on day 0 and day 25±3” was modified to “the participants will receive a third dose of recombinant protein subunit vaccine 6 months after completing their two-dose regimen of inactivated COVID-19 vaccine.” | Due to the current pandemic, the national public health policy now mandates the administration of a third booster dose for vaccination. |
|  |  | **Follow-up time adjustment:**  Follow-up assessments are scheduled at the 1^st^, 3^rd^, 6^th^, and 9^th^ months following the administration of the two vaccine doses. The timing was adjusted to the 1^st^, 2^nd^, 4^th^, 7^th^, 8^th^, 10^th^, 13^th^, and 16^th^ months after the initial vaccine dose. | We need to conduct follow-up assessments in the 1^st^, 3^rd^, 6^th^, and 9^th^ months following the final vaccination to assess its safety and immune protection. |
| 2.0 (Final) | January 26, 2022 | **Items of laboratory test adjustment:**  Blood routine, liver and kidney function, blood glucose, blood lipids, and coagulation function will be tested at each follow-up point, adjusted to only test liver and kidney function, blood sugar, and blood lipids starting from the 7^th^ month (3^rd^ dose of vaccination). | The primary objective of performing blood routine and coagulation function tests is to assess safety post-vaccination. Following the initial two vaccine doses, no adverse reactions associated with coagulation or blood count were observed among the participants. The majority of the project participants are elderly individuals who are resistant to frequent and extensive blood collection, consequently leading to a reduced willingness for follow-up. To ensure compliance with follow-up procedures, the blood routine and coagulation function tests were omitted without compromising the scientific integrity of the project. |

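### The Full Analysis Set is labelled intention-to-treat but defined as three-dose completers, so pre-booster immunogenicity and the baseline table cover only people who later took dose 3

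*Protocol*

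**What the plan says.** Protocol section 3.10.1 opens the FAS definition with a principle: "According to the intention-to-treat (ITT) principle, this study aims to include as many participants as possible". The next sentence is a restriction: "Participants who did not complete all three doses of vaccination will be excluded".

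The other two sets are defined in the same section:
- Per-Protocol Set (PPS): "Based on the FAS population, participants with poor compliance will be excluded". It sits inside the FAS and carries the same restriction.
- Safety Set: "Participants with at least one vaccination record and measured AEs/SAEs correspondingly". One dose is enough, and the three-dose rule does not apply.

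Section 3.10.2 allocates the analyses. Safety, the primary endpoint, uses the Safety Set. For the antibody endpoints, "the secondary analysis (immunogenicity) will be performed both in the FAS and PPS population". For the comparison of the age groups at entry, "The analysis of baseline demographic information will be based on the FAS population".

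Sections 3.3.2 and 3.5 put dose 3 six months after dose 2, at V5 (month 7). Section 3.4.2 lists antibody titres at baseline and at months 1, 2, 4, 7, 8, 10, 13 and 16.

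**The concern.** The two sentences of the FAS definition cannot both hold. A set that drops everyone without the full course is a completers' set, whatever its label. A reader told that the FAS follows intention-to-treat will take its results as describing everyone who entered and started vaccination.

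The practical problem lies at the visits before the booster. Someone with two doses and valid titres at months 1, 2 and 4 is removed from all three visits for not receiving an injection due at month 7. The estimates of response to the two-dose inactivated course are then conditional on a later event. Section 3.3.3 lists want of efficacy, intolerance, adverse events, poor compliance and investigator judgement among the reasons for leaving. Completion may therefore be related to response, and possibly to a different degree in the two age groups.

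The baseline table has a related fault. It describes three-dose completers, while the primary safety analysis covers anyone with at least one dose and the corresponding adverse-event record. People who stopped early count in the primary analysis but are missing from the table meant to show whether the groups are comparable.

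**Working it through.** The point concerns a definition, and the protocol states no figure for it to reproduce. The sample-size section gives only 200 + 100 = 300, a 2:1 split, which is consistent. It gives no non-completion rate, effect size or SD.

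**Step 1: which visits are conditioned on a later event.**

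| Antibody visit | Relation to dose 3 | Effect of the FAS rule |
| --- | --- | --- |
| Baseline | Before | Restricted to later completers, but no vaccine response exists yet |
| Months 1, 2, 4 | Before | Response restricted to later completers |
| Month 7 (V5) | Same visit | Restricted to later completers if blood is drawn first; the order is not stated |
| Months 8, 10, 13, 16 | After | Cohort defined by a past exposure |

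Of nine sampling points, three post-baseline points are certainly affected, and four if month 7 blood precedes the dose.

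**Step 2: whether another planned set escapes.** Immunogenicity uses the FAS and PPS only, and the PPS is a subset of the FAS. By definition, everyone contributing at months 1, 2 and 4 later received dose 3. Comparing FAS with PPS results cannot reveal the effect, because both sets share the restriction.

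**Step 3: scale, with assumed inputs.** Let d be the share of an age group without dose 3, and δ the mean difference, completers minus non-completers, in SD units of a suitably transformed titre.

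All-participant mean = (1 − d) × completer mean + d × (completer mean − δ) = completer mean − dδ.

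The completer-only mean is therefore off by dδ, and the elderly–young difference by (d_elderly − d_young) × δ if δ is the same in both groups.

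- Numbers: with d = 5%, 10%, 20% or 30% in both groups, the set falls from 200/100 to 190/95, 180/90, 160/80 or 140/70.
- One group: 0.05 × 0.25 = 0.0125 SD up to 0.30 × 0.5 = 0.15 SD.
- Positive rate, assuming 90% in completers and 70% in non-completers: 0.05 × 20 = 1 up to 0.30 × 20 = 6 percentage points.
- Elderly–young difference:

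| d elderly / young | δ = 0.25 SD | δ = 0.5 SD |
| --- | --- | --- |
| 10% / 5% | 0.0125 | 0.025 |
| 20% / 5% | 0.0375 | 0.075 |
| 30% / 10% | 0.05 | 0.10 |

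For comparison, the standard error of the difference at 200/100 is √(1/200 + 1/100) = 0.122 SD. Every illustrated shift lies below one standard error. Unlike the standard error, the shift does not shrink as the sample grows. With δ = 0 it is zero and only numbers are lost; with δ negative its sign reverses. The plan compares absolute titres by medians and the Mann–Whitney test, so these mean shifts indicate scale and do not predict the planned statistics.

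**The case against.** The intervention is the three-dose sequence, so a three-dose population is a legitimate one for describing results after the booster. Groups are formed by age, so there is no randomised comparability for intention-to-treat to protect. Immunogenicity is a secondary endpoint. All of this stands. It limits the weight of the point and argues for keeping the completers' set after dose 3, but it does not justify using that set before dose 3 or calling it intention-to-treat.

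Inclusion criterion 3 also matters: it asks for six months or more of completed follow-up. Applied literally, it already removes early leavers, and the three-dose rule then takes out only people who reached six months and missed dose 3 at about month 7. That narrows the rule's own contribution. It also means that changing the FAS alone would leave similar selection in place.

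Four stronger readings are tempting, and the protocol does not support them.
- **Breakthrough infection.** "The population for breakthrough infection analysis will be based on the FAS population", so a reader might infer that it too is conditioned on the future. The outcome concerns the end of 2022. Seven months after the listed enrolment date of July 2021 is about February 2022, so for people enrolled near that date dose 3 comes first. That is selection on a past exposure.
- **PPS and pseudovirus subset.** A reader might think the rule materially changes these. The PPS drops anyone with six or fewer follow-ups; a person leaving at month 7 has at most four post-baseline visits (V2–V5), or five counting V1. The pseudovirus subset requires complete data at baseline and months 2, 7, 8, 13 and 16. Early leavers are out of both anyway.
- **Inflated titres.** A reader might infer that the rule raises titres, especially in the elderly. The protocol gives neither the rate of non-completion nor the direction of any difference.
- **The amendment.** The revision history changes the plan so that "the participants will receive a third dose of recombinant protein subunit vaccine 6 months after completing their two-dose regimen of inactivated COVID-19 vaccine". One might infer that people enrolled for two doses then declined a third. The entry is dated March 2020, before the listed enrolment date, so the document does not show this.

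**Conclusion.** The protocol contradicts itself: the FAS is called intention-to-treat and defined as three-dose completers. As a result, titres and positive rates at months 1, 2 and 4, possibly month 7, and the baseline table describe only people who went on to receive dose 3, and no planned immunogenicity set avoids this. These conclusions follow from the definitions and need no assumption.

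Whether the estimates are biased, by how much and in which direction cannot be determined from the protocol. The exit reasons make informative selection plausible, no more. The illustrated shifts rest on assumed non-completion of 5% to 30% and an assumed difference of 0.25 to 0.5 SD. The primary safety analysis is not touched. The fault is confined to secondary and descriptive results, but it affects how they will be read and can be corrected with data already collected.

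**What to change.** - Define the FAS as all participants with at least one dose and at least one post-baseline antibody result.
- Analyse each pre-booster visit in everyone who received the doses due by that visit. State whether blood at month 7 is drawn before or after the injection, so that the visit can be classified.
- Keep the present set under the name three-dose completers for months 8–16, and show the wider FAS alongside it with the number boosted.
- Base the demographic table on the wider set.
- Reconcile inclusion criterion 3 with the new FAS. As written it conditions entry on later follow-up, so the wider set would still be selected in the same way.

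The cost is a paragraph of protocol or SAP wording and a rerun of tables, with somewhat more missing data at the late visits of the wider set. No new data are needed.

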### 3.3.2. Intervention assignment

Both the experimental and control groups will receive two doses of the inactivated COVID-19 vaccine, administered on day 0 (baseline) and day 25±3. A third booster dose will be given 6 months after the second dose.

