### 3.4.2 Secondary endpoint measures

- Immune protection of the participants:
  - - The titers of neutralizing and anti-receptor binding domain (RBD) antibodies at the baseline and the 1^st^, 2^nd^, 4^th^, 7^th^, 8^th^, 10^th^, 13^th^, and 16^th^ months after the first vaccination in each study group.

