**Secondary analysis:**

The secondary endpoint of this study is the immunogenicity after vaccination, which is performed on the FAS and PPS.

The antibody-positive rates at each follow-up point in the two groups will be statistically described as categorical variables, and Pearson’s chi-square test or Fisher’s exact test will be used for intergroup comparisons. The antibody titers at each follow-up point in the two groups will be statistically described as continuous variables, and the Mann–Whitney U test will be employed for intergroup comparison. For the absolute titers of neutralizing antibodies and anti-RBD antibodies, the median values of antibody titers will be calculated for the two groups at each follow-up point, as well as the corresponding intergroup differences and 95% CIs. For the relative titer values of variant-specific neutralizing antibodies, the geometric mean of the antibody titers for the two groups will be determined at each follow-up point, as well as the corresponding intergroup differences and 95% CIs.

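### The Per-Protocol Set defines compliance only as a visit count, so it keeps off-schedule dosing and sampling and removes on-schedule participants from every time point

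*Protocol*

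**What the plan says.** Protocol section 3.10.1 restricts the FAS as follows: "Participants who did not complete all three doses of vaccination will be excluded". It sets no condition on when the doses were given. The PPS is a subset: "Based on the FAS population, participants with poor compliance will be excluded". The next sentence gives the specific meaning of that exclusion: "this set excludes individuals who participated in follow-up no more than six times". No other condition is added, and missing immunogenicity data are not imputed.

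The schedule that a per-protocol set would normally reflect is elsewhere. Section 3.3.2 has the first two doses "administered on day 0 (baseline) and day 25±3" and adds: "A third booster dose will be given 6 months after the second dose". The table in section 3.5 puts vaccination at V1, V2 and V5 and gives each visit from V1 to V9 a window in days. Section 3.4.2 lists titres at baseline and at eight later points, counted in "months after the first vaccination in each study group".

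Section 3.10.2 uses both the FAS and the PPS for immunogenicity, point by point: "The antibody titers at each follow-up point in the two groups will be statistically described as continuous variables". The separate breakthrough analysis starts from the FAS and will "exclude participants whose SARS-CoV-2 infection status during the end of the 2022 pandemic cannot be confirmed through follow-up". Infection status plays no part in the PPS.

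**The concern.** A per-protocol set should show whether the result holds in participants who were treated and measured as planned. This one uses number of attendances as a substitute for that. Dose interval, sample timing and eligibility do not enter.

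The rule therefore errs in two ways. It admits people whose titres were not produced or measured on the planned schedule. It also deletes valid early titres because other visits were missed, although the analysis is done separately at each visit and a missed month 16 says nothing about the quality of a month-8 sample.

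Attendance may also differ by age group, which is the comparison of interest. Section 7.1 gives reluctance among the mostly elderly participants to undergo frequent blood collection as a reason for cutting tests. The protocol gives no attendance figures by group, so the direction of any resulting bias is unknown.

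**Working it through.** There is no plan figure to reproduce: the protocol states no PPS size, attendance rate or power calculation. The target of 200 + 100 = 300 adds up.

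**1. Visits that can be counted.** Sections 3.4.2 and 3.5 give months 1, 2, 4, 7, 8, 10, 13 and 16 (V2 to V9), which is 8 follow-ups, or 9 if V1 counts. The protocol does not say which. More than six means at least 7.

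**2. The rule applied to participants with all three doses on schedule.**
- Counting V2 to V9, a participant complete to month 10 has 6 follow-ups and is removed at all time points, including month 2 (after dose 2) and month 8 (after dose 3).
- Counting V1 as well, a participant complete to month 8 has 6 and is removed in the same way.
- Under either count, a participant with three doses at any interval and at least 7 attendances stays in, whatever the sample dates.

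**3. Share of three-dose participants removed.** Assume that FAS members attended the dosing visits (V1, V2, V5) and attended each of the other six independently with probability p. The values of p are assumptions.
- 8 visits counted: V2 and V5 supply 2, so at least 5 of 6 are needed. Retained = p^6 + 6p^5(1−p).
- 9 visits counted: V1, V2 and V5 supply 3, so at least 4 of 6 are needed. Retained = p^6 + 6p^5(1−p) + 15p^4(1−p)^2.
- At p = 0.90: 0.5314 + 0.3543 = 0.8857, so 11.4% are removed. Adding 0.0984 gives 0.9842, so 1.6% are removed.
- At p = 0.85: 0.3772 + 0.3993 = 0.7765, so 22.4% are removed. Adding 0.1762 gives 0.9527, so 4.7% are removed.

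| p | Removed, 8 counted | Removed, 9 counted |
|---|---|---|
| 0.80 | 34.5% (103 of 300) | 9.9% (30) |
| 0.85 | 22.4% (67) | 4.7% (14) |
| 0.90 | 11.4% (34) | 1.6% (5) |
| 0.95 | 3.3% (10) | 0.2% (1) |

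The counts suppose that all 300 are in the FAS.

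**4. Month-8 samples discarded.** Some of those removed would have had no month-8 sample anyway. Among those who attended month 8, the 8-visit count requires at least 4 of the other 5 free visits. Retained = p^5 + 5p^4(1−p). At p = 0.90 this is 0.5905 + 0.3281 = 0.9185, so 8.1% of available month-8 samples are lost. At p = 0.85 it is 0.4437 + 0.3915 = 0.8352, so 16.5% are lost.

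**5. Dose timing as stated in two places** (month = 30.44 days).
- Dose 2: section 3.3.2 gives days 22 to 28. Section 3.5 gives month 1 ± 3 days, about days 27 to 33.
- Dose 3: six months after dose 2 is about days 205 to 211. Section 3.5 gives month 7 ± 3 days, about days 210 to 216.

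The ranges barely overlap, so a timing criterion cannot be applied until they are reconciled.

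**6. Month 16 in calendar time.** Section 1 gives one enrolment date, July 1, 2021. Sixteen months later is about October 31, 2022, with a window of October 16 to November 15. The end of recruitment is not given.

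**The case against.** The strongest reply is that little depends on the PPS. Immunogenicity is a secondary endpoint and is also analysed in the FAS without imputation, so the participant complete to month 10 still contributes month-2 and month-8 titres there. The primary safety analysis uses the Safety Set. This stands, and it limits the size of the point.

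A second reply is that a fixed set across visits helps to describe waning. That is reasonable, but the rule does not deliver it. Someone with 7 of 8 visits may miss month 8 and remain, so the participants measured still change from visit to visit.

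A third is that section 3.3.3 lists inability to be vaccinated on schedule as an exit reason, and that deviation rules can be left to an SAP. The exit clause is permissive and is not an analysis-set rule. The protocol has also not left compliance open; it has fixed its meaning.

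Two overstatements should be avoided. A reader might treat all eight visits as missable and compute 18.7% removed at 90% attendance and 34.3% at 85%. Those figures ignore that FAS members received all three doses and so should have attended the dosing visits. A reader might also say that the rule tests late attendance. It counts any visits, and an early miss weighs the same as a late one.

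**Conclusion.** The point holds as a badly fixed definition in a supporting analysis. As written, PPS membership says nothing about dose timing, sample timing or eligibility, and it removes on-schedule participants from visits they attended. The removal is about 11% to 22% of three-dose participants at 90% to 85% attendance if 8 visits count, and about 2% to 5% if 9 count. These figures rest on assumed attendance rates, independence between visits and attendance at dosing visits. The ambiguity over V1 alone changes the share removed several-fold. The rule should be changed, but it does not affect the FAS result or the primary safety analysis.

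A reader might infer that the PPS is contaminated by titres raised by infection at month 16. The documents do not show this. No rule excludes a titre taken after infection, but the one enrolment date given puts month 16 at mid-October to mid-November 2022. Overlap with the end of 2022 needs later enrolment, whose extent is not stated, so the number of affected samples is unknown. Likewise, the possibility that breakthrough analyses (4) and (5) pair an infection with a later titre is a separate matter. Those analyses use the FAS and are not caused or cured by the PPS definition.

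**What to change.** Drop the visit count and define the PPS visit by visit. A participant contributes at a visit if eligibility was met, every dose due by that visit was given within the protocol's windows, and the sample was taken within its visit window. First reconcile the dose-timing statements in sections 3.3.2 and 3.5; this review does not say which is right.

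Conditional addition: where a known infection precedes a sample, leave that titre out of the PPS and out of an added FAS sensitivity analysis. In breakthrough analyses (4) and (5), use the last titre before infection. This needs infection dates. The protocol describes infection status and symptom duration but no date field, so check first that dates were collected.

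Cost: a change of definition and a derivation from dose and sample dates, with no new procedures for participants. The drawback is that the PPS size will vary by visit. If a fixed group is wanted for describing waning, add a summary in complete attenders and label it as such.

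### Late-visit titre comparisons use only three-dose recipients who attended and ignore their earlier titres, so they can be biased if missing a visit is related to earlier titre

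*Protocol*

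**What the plan says.** Three statements in the protocol combine here.

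- **Missing data (section 3.10.1):** "The missing data on demographic information, safety indicators, and immunogenicity indicators for the FAS and PPS populations will not be imputed".
- **Analysis set (same section):** for the FAS, "Participants who did not complete all three doses of vaccination will be excluded". The PPS is the FAS without those who attended six or fewer follow-ups.
- **Titre analysis (section 3.10.2, Secondary analysis):** "The secondary endpoint of this study is the immunogenicity after vaccination, which is performed on the FAS and PPS". Then "The antibody titers at each follow-up point in the two groups will be statistically described as continuous variables", the Mann-Whitney "U test will be employed for intergroup comparison", and "the median values of antibody titers will be calculated for the two groups at each follow-up point", with differences between groups and 95% CIs.

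The other methods in section 3.10.2 are paired and nested t-tests, the Wilcoxon test, correlations, and logistic regression on baseline characteristics. None of them brings a participant's earlier titres into a late-visit comparison of the age groups. No missing-data sensitivity analysis is named.

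Section 7.1, explaining the version 2.0 change, says of attendance at follow-up visits: "The majority of the project participants are elderly individuals who are resistant to frequent and extensive blood collection, consequently leading to a reduced willingness for" (the quotation stops one word short of the end of the sentence). The response was to drop the blood routine and coagulation tests from month 7.

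**The concern.** Not imputing is a sound choice when the analysis uses each person's whole record. A likelihood-based mixed model imputes nothing either. The difficulty is the combination of no imputation with a separate two-sample test at each visit. A participant with titres at months 1 to 8 who is absent at month 13 contributes nothing to the month-13 comparison, although the earlier values say a good deal about the missing one.

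The per-visit comparison is therefore unbiased only if, within each age group, absence is unrelated to titre. The stated objective concerns people aged 60 to 80, not those of them who were still being bled at month 13 or 16. If attenders and non-attenders differ in earlier titre, the late age-group differences and the apparent rate of waning mix a real effect with a change in who is being measured.

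This is separate from the definition of the FAS. It arises inside the FAS, among people who received all three doses.

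**Working it through.** **What is at hand.** The protocol gives 200 elderly and 100 young participants (section 3.6) and eight post-baseline visits, at months 1, 2, 4, 7, 8, 10, 13 and 16 (sections 3.4.2 and 3.5). It gives no titre SD, effect size or dropout rate, so there is no stated figure to reproduce. What follows illustrates a mechanism under assumptions.

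**Step 1: bias when there is no true age difference.** Assumptions, not from the protocol: log10 titre SD 0.5; correlation r between the earlier and the late visit of 0.5 or 0.7; young group fully observed; elderly missingness as tabulated.

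- Standardised titres: late = r × earlier + √(1 − r²) × independent noise.
- P(missing) = 1/(1 + exp(−(m − ln(OR) × earlier))), with m set to give the stated fraction missing. OR is the factor by which the odds of missing rise per SD lower earlier titre.
- Attender-only ratio = 10^(0.5 × median late value among attenders).
- Estimate using the earlier visit = mean late value of attenders + slope × (mean earlier value of all − mean earlier value of attenders).

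The true elderly/young ratio is 1.00. Attender-only ratios:

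| Elderly missing | OR 1 | OR 2, r 0.5 | OR 2, r 0.7 | OR 3, r 0.5 | OR 3, r 0.7 |
|---|---|---|---|---|---|
| 10% | 1.00 | 1.04 | 1.05 | 1.06 | 1.08 |
| 20% | 1.00 | 1.08 | 1.11 | 1.11 | 1.15 |
| 30% | 1.00 | 1.11 | 1.17 | 1.17 | 1.24 |
| 40% | 1.00 | 1.16 | 1.23 | 1.23 | 1.32 |

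For example, at 20% missing, OR 2 and r 0.7 the bias is +0.044 log10, and 10^0.044 = 1.11. The estimate that uses the earlier visit returns 1.00 in every cell. If high responders are the ones who stay away, the direction reverses.

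**Step 2: effect on the test.** With 200 v 100, r 0.7 and 2,000 simulated trials per case, the nominal 5% Mann-Whitney test rejects a true null in 4.4% (20% missing, OR 1), 11% (20%, OR 2), 18% (30%, OR 2), 29% (30%, OR 3) and 43% (40%, OR 3).

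**Step 3: bias when there is a true gap.** Assumptions: SD 0.45; gap −0.15 log10; correlation 0.6 to 0.8; 20% to 30% missing in the elderly and 10% in the young; 3,000 simulated trials per case.

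- OR 1: no bias, within about 1%.
- OR 1.35: median gap about 5% to 14% too small.
- OR 2: about 11% to 31% too small.
- Using the earlier titre: within about 1% of the true gap throughout.

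**Step 4: precision.** At SD 0.45 with 140 v 90 observed (30% and 10% missing):

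- SE of a difference in means = 0.45 × √(1/140 + 1/90) = 0.061.
- SE of a difference in medians, normal data = 0.061 × √(π/2) = 0.076.
- Complete data, means = 0.45 × √(1/200 + 1/100) = 0.055.

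Using the earlier visit gave 0.056 to 0.059 in step 3. Most of the fall from 0.076 thus comes from replacing medians by means, and only a little from the earlier titres.

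**Step 5: do other planned analyses cover this?** A PPS member has attended at least seven follow-ups, so has missed at most 8 − 7 = 1. The pseudovirus subset requires no missing values at baseline and months 2, 7, 8, 13 and 16. Both hold membership nearly or fully fixed, which limits drift from visit to visit, but they do so by selecting on attendance.

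**The case against.** The strongest reply is that the protocol does not show the condition that bias requires. Section 7.1 speaks of resistance to frequent and extensive blood collection. It gives no rates, no comparison with the young group and no link to titre. Heavier loss in one group alone causes no bias, as the OR 1 results show. The cited sentence also justifies a remedy: fewer tests from month 7, before the visits at months 10 to 16. All of this stands.

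A reader might infer that the elderly will be lost more often than the young, or that frailer, lower responders will leave so that the age gap is understated. The protocol supports neither. A reader might also assume that titres up to month 8 are largely known. FAS membership requires three doses, the last at month 7, but not a month-8 sample, and no attendance rate is given.

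The illustrations also favour the model. The data are normal, the earlier titre is always observed, missingness is at random given that titre, and no values lie below the assay limit. The upper figures come from the more extreme corners. This limits what the magnitudes can carry.

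It could finally be said that the analysis plan, which is not shown, may supply the model. But the protocol itself fixes per-visit tests without imputation, so this is a stated choice and not a gap left for later.

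**Conclusion.** The point holds in conditional form. As written, the late-visit comparisons describe three-dose recipients who attended, discard their earlier titres, and are biased if absence depends on those titres within an age group. There is no bias if absence is unrelated to titre, and the protocol settles neither size nor direction. Under the assumptions above, the distortion runs from nil to about 32% in the titre ratio when there is no true difference, or from nil to about 31% of a true gap of 0.15 log10.

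Two stronger claims should not be made. The sentence on imputation is not in itself an error. Nor should a large gain in precision be claimed, because most of it comes from changing the summary measure.

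Titres are the secondary endpoint and the primary safety analysis is untouched. This is a worthwhile and inexpensive improvement, not a fault that undermines the trial.

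**What to change.** In section 3.10.2, Secondary analysis, add for the FAS a likelihood-based repeated-measures model of log neutralizing and log anti-RBD titre over all post-baseline visits. Include age group, visit, their interaction and a within-person covariance. Report the geometric mean ratio between groups with its 95% CI at each visit, and base the late-visit comparisons on it.

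- Keep the per-visit Mann-Whitney tests and medians as a check on the distributional assumption. They are not a missing-data sensitivity analysis, because they need the stronger assumption about absence.
- State how values below the assay limit are handled, either as censored or by a named substitution.
- Add a simple sensitivity analysis for data missing not at random, such as a shift applied to missing late titres. The model does not remove bias that depends on the unseen late titre itself.
- In section 3.10.1 the no-imputation rule can stay for the main model. State the missing-at-random assumption beside it and exempt the shift analysis.

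The cost is one extra model, which the named software can fit, a short sensitivity analysis, and an assumption of roughly normal log titres. The reported effect also changes from a difference in medians to a ratio of geometric means. No new visits, samples or participants are needed.
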